   1. PRIMARY OBJECTIVE

Our study aims to evaluate the usability and potential benefits of the structured use of patient-reported outcome measures (PROMs) and patient-reported experience measures (PREMs) to improve care for patients with chronic diseases in Germany.

**Main research question:**

Can digital PROMs (ePROMs) and digital PREMs (ePREMs) be used in patients with chronic diseases for quality measurement at the health system level (e.g., for health-system performance assessment (HSPA))?

- How representative are response rates in patients with chronic diseases via digital surveys?
- How do response rates and willingness to respond multiple times vary over time by age, gender, indication, city/state, health system use (frequent versus infrequent users), web- or app-based surveys, and Disease Management Program (DMP) participation?
  1. SECONDARY OBJECTIVES

1. To what extent can value of care variation in care be identified from ePROMs and ePREMs surveys?

- What is the share of suspected low-value care and suspected high-value care in Germany, per indication and in subgroups?
- How do ePROM and ePREM results differ according to age, gender, indication, city/state, healthcare system utilization (changes in frequency of outpatient practitioner attendance, prescriptions, hospitalizations, etc.), and DMP participation?
- Can ePROMs and ePREMs function as an early warning signal for deteriorating chronic conditions or adverse events such as hospital admission?

1. What are the benefits or drawbacks of PRO feedback (outcome reports) sent to patients?

- Are the PRO value reports understandable to patients?
- Can PRO feedback function as a positive nudge (lead to positive behavioral changes e.g., healthier or more active lifestyle, more active participation in medical treatment, actively approaching treating physicians in the office setting)?
- Are there any negative emotional reactions when receiving PRO feedback that shows values worse than those of a comparable group?

1. Background/Introduction

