   1. STUDY DESIGN

The study is an observational prospective cohort study with patients of four chronic disease areas with existing DMPs (asthma, chronic obstructive pulmonary disease (COPD), diabetes (type 1 and type 2) and coronary artery disease) with two sub-cohorts (DMP and non-DMP) for each disease.

- Type of control: none / group matched BARMER insurees (matching criteria: disease area, gender, age group)
- Level and method of blinding: none
- Method of treatment assignment: stratified randomized selection of study population
- Number of subjects: 200,000 patients invited (50,000 per chronic indication and about 25,000 in each sub-cohort)
- Duration of study: one year (four quarterly survey periods)

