  1. STUDY POPULATION

Inclusion criteria:

- Patient is at least 18 years old
- At least two outpatient consultations documenting a confirmed chronic disease diagnosis in 2021
- For type 1 diabetes at least one insulin prescription must be present in 2021

Exclusion criteria:

- Participation in more than one DMP

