  1. INTERVENTION

In addition to filling out the survey questions at four points in time (intervention 1), all participants will receive PRO feedback as a potential nudge (intervention 2). The PRO feedback will be a pdf report sent via email and available in their study participant profile, which graphically (line charts) shows the patients’ individual generic and disease-specific health status in comparison to the individual peer group. In addition to the visual feedback, the results will shortly be explained on the same page. The description will cover whether patient-individual PRO scores are better or worse compared to the peer group, and for longitudinal values, whether patient-related changes improved or worsened. Additional details on the scores, sub-scores, and calculations are shared with the patients on the following pages of the report. Peer groups are classified according to their disease, gender, and age group. The peer group is created based on individuals who have replied to the previous survey and will only be displayed if the group consists of at least four individuals. This threshold is set by the German General Data Protection Regulation. The report refers to the patients’ physicians as the main contact to discuss the results or in case of questions.

- 1. SAMPLE SIZE

The sample is drawn stratified randomly from insured patients of one large German statutory health insurance with about 9 million insured persons (of about 73 million statutorily insured persons in total in Germany) according to their diagnosis and/or disease management program status. A one-to-one matching of participants of one DMP with non-participants of a DMP but with the same proven diagnosis according to the ICD-10-GM system is made. Further stratification criteria are age group, gender, and health system utilization.

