An initial invitation letter is sent to 200,000 insured individuals, 50,000 of each of the selected chronic conditions (about 25,000 per sub-cohort). Diabetes type 1 and type 2 are considered jointly as there is no differentiation in the selected PROMs. The patients of all chronic diseases are allocated to groups based on their participation in DMP (DMP or non-DMP group). Prior experiences suggest that around 30% of patients react to invitations to participate in research by their insurer [29-31]. Two-thirds of initial participants are expected to allow follow-up contacts and around 40% of these patients will continue participating in all the follow-up surveys after receiving reminders for each task. Therefore, after accounting for non-participants and participants with no complete survey data we expect a complete data set for 16,000 participants. However, the first research question will investigate response rates as there is no evidence on this population yet.

- 1. STUDY PROCEDURE

Eligible participants will be participating in the study for a maximum of four quarters, starting with the first access of the digital questionnaires followed by quarterly digital surveys split into several tasks. To start the survey, participants register with their study pseudonyms and share personal information, e.g., basic demographics and identification data. Each survey period contains four tasks to be completed by participants defined as sets of questions that each will take five to ten minutes to complete. The participants are invited to answer PROM and PREM surveys.
[figure not shown]

*Figure 1: Study design: Participants’ timeline and tasks*

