Based on the combination of PROMs, PREMs and health care system utilization measured as costs, a value-based healthcare cube is introduced. PROM and PREM scores function as outcome dimensions and healthcare system utilization as cost dimension. Costs are hence added as new axis inside the framework (see Figure 5).

[figure not shown]

*Figure 5: Assessment of Value-Based Healthcare - Framework*

The newly introduced value-based healthcare cube allows the measurement of high-value and low-value care. Along the previously defined areas of suspected high- and low-value care (see Figure 4 and 5), the cube can be subdivided into 27 segments (see Figure 6). High-value and low-value care will be investigated based on the following criteria:

- High-value indication in both dimensions (high patient-relevant indicators (PROMs/PREMs) **at** low costs) (Figure 6 – dark green area)
- High-value indication in at least one dimension (high patient-relevant indicators (PROMs/PREMs) **or** low costs) (Figure 6 – light green area)
- Low-value indication in at least one dimension (low patient-relevant indicators (PROMs/PREMs) **or** high costs) (Figure 6 – light red area)
- Low-value indication in both dimensions (low patient-relevant indicators (PROMs/PREMs) **at** high costs) (Figure 6 – dark red area)

The value of care dimensions will be summarized into high- versus low-value care as the broad definition and into high two-sided, high one-sided, low one-sided and low two-sided value care as narrow definition. For both categorizations the frequency as well as the variation per subgroups (e.g. region, DMP etc.) will be analyzed.

[figure not shown]

*Figure 6: Assessment of Value-Based Healthcare – Framework distinguishing between high- and low-value care*

*Outcome and experience variation*

Mean change in PROM and PREM-index (sub-)scores overall and per subgroup (see 5.1 and 4.3) per disease area over time:

- Average per survey period
- Consistency over time (test-retest reliability)

Meaningful change / Minimally clinical important difference (MCID) in PROM index (sub-)scores overall and per subgroup (see 5.1 and 4.3) per disease area over time:

- Average per survey period
- Consistency over time (test-retest reliability)

*Hospital admission risk based on PROMs/PREMs and patient characteristics*

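### Research question 2 asks for value-of-care shares in Germany, but the draw is one insurer with DMP and non-DMP patients invited about 50:50, and no weighting is stated for these shares or their reference averages

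*Protocol*

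**What the plan says.** **Target.** Protocol section 1.2 poses the question: "What is the share of suspected low-value care and suspected high-value care in Germany, per indication and in subgroups". This is a population prevalence, wanted for each disease and within subgroups.

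**Frame.** Section 2.5: "The sample is drawn stratified randomly from insured patients of one large German statutory health insurance with about 9 million insured persons", out of about 73 million statutorily insured. Section 2.3 excludes patients with "Participation in more than one DMP".

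**Draw.** Section 2.1 gives "200,000 patients invited (50,000 per chronic indication and about 25,000 in each sub-cohort". Section 2.5 adds "A one-to-one matching of participants of one DMP with non-participants of a DMP but with the same proven diagnosis", and then: "Further stratification criteria are age group, gender, and health system utilization".

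**Weighting.** Sections 4.1 and 5.2 (primary outcomes) plan to weight participants to the target population when representativeness is judged. Section 4.1 names gender, age and diagnosis; section 5.2 adds utilization. DMP status is not named in either place. The target there is the insurer's population.

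**Value-of-care analysis.** Section 5.2 (secondary outcomes) classifies each patient against an average, with a standard deviation in Table 1 and in the cost classes, over at least two survey periods. It then says: "For both categorizations the frequency as well as the variation per subgroups (e.g. region, DMP etc.) will be analyzed". It mentions no weights and does not name the population behind the average.

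**The concern.** The draw is disproportionate on DMP status by design. Within each disease about half of those invited are DMP members, whatever the enrolment rate among insured patients with that disease. A frequency counted in such a sample equals the population share only if the population also splits evenly or the two sub-cohorts have the same share.

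The classification rule adds a second route. If the average and standard deviation come from the participants, the DMP mix sets the reference point. A patient with unchanged scores can then move in or out of the low-value group because the mix of the sample changed.

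At stake are the per-disease and subgroup shares that answer research question 2. A larger sample does not remove an error of this kind. Weighting to the insurer would still leave a gap to Germany as a whole.

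**Working it through.** **Inputs from the protocol.** 200,000 invited; 50,000 per disease; about 25,000 per sub-cohort (section 2.1). Section 2.5: "Prior experiences suggest that around 30% of patients react to invitations to participate in research by their insurer"; two-thirds then allow follow-up, about 40% of those complete all surveys, and 16,000 complete data sets are expected.

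**Inputs not in the protocol, so assumed.** True DMP share q per disease (20% to 80%), low-value shares by sub-cohort, standardized difference between sub-cohorts, correlation between survey periods.

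**1. The plan's own figure.** 200,000 × 0.30 × 2/3 × 0.40 = 16,000, which agrees. The quotas also add up: 4 × 50,000 = 8 × 25,000 = 200,000. With equal response and retention this gives 16,000/4 = 4,000 completers per disease and 2,000 per sub-cohort.

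**2. Fixed cut-off.** Sample share = 0.5·p_DMP + 0.5·p_nonDMP. Population share = q·p_DMP + (1 − q)·p_nonDMP. The difference, sample minus population, is (0.5 − q)(p_DMP − p_nonDMP).

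| p_DMP / p_nonDMP | Sample, 50:50 | Population, q = 20% | Population, q = 50% | Population, q = 80% |
|---|---|---|---|---|
| 15% / 15% | 15.0% | 15.0% | 15.0% | 15.0% |
| 15% / 20% | 17.5% | 19.0% | 17.5% | 16.0% |
| 12% / 22% | 17.0% | 20.0% | 17.0% | 14.0% |
| 10% / 25% | 17.5% | 22.0% | 17.5% | 13.0% |

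The error runs from 0 to 4.5 points in either direction. For scale, the 95% half-width of a 17.5% share at 4,000 completers is 1.96 × √(0.175 × 0.825 / 4,000) = 1.2 points.

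**3. Cut-off relative to the sample mean.** Simulation with 400,000 patients per setting, four periods, normal scores and ICC 0.7. The DMP mean lies d within-sub-cohort SDs above the non-DMP mean. Low value means more than one sample SD below the sample mean in at least two of four periods. This cut-off is itself an assumption, because the running text of section 5.2 and Table 1 word the rule differently.

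| d | DMP fraction | Pooled low | DMP low | Non-DMP low |
|---|---|---|---|---|
| 0.3 | 20% | 17.6% | 11.4% | 19.2% |
| 0.3 | 50% | 17.6% | 13.3% | 21.9% |
| 0.3 | 80% | 17.5% | 15.7% | 25.0% |
| 0.6 | 20% | 17.6% | 6.6% | 20.3% |
| 0.6 | 50% | 17.7% | 9.5% | 25.9% |
| 0.6 | 80% | 17.6% | 13.7% | 33.2% |

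The pooled share hardly moves, because the rule itself fixes it. The sub-cohort shares move with the mix although the score distribution within each sub-cohort is unchanged. With d = 0 all shares stay at 17.5% to 17.7%.

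**4. Disease quotas.** These drop out of any share reported per disease. They enter only a share pooled over the four diseases.

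**5. Price of reweighting DMP status.** The weights are 2q for DMP and 2(1 − q) for non-DMP patients, so the Kish design effect is 2(q² + (1 − q)²). At q = 20% or 80% it is 2 × (0.04 + 0.64) = 1.36. Then 4,000 completers carry the information of 4,000/1.36 ≈ 2,940, and intervals widen by √1.36 ≈ 1.17.

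**The case against.** The strongest objection is that section 5.2 does not use a fixed cut-off. If its average is the participants' own average, the pooled share per disease is set by the rule and not by the quota, as step 3 confirms. A constant bias of a few points in that share is therefore not established. This stands. It does not cover the sub-cohort shares, which the same section says will be reported.

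Second, all enrolment and category rates above are assumed, the error vanishes at q = 50% or with equal sub-cohorts, and the 50:50 split applies to invitations. Section 1.1 leaves response by DMP participation open, so completers may split differently. This also stands, and it is why the size can only be given as a range.

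Third, weights for a secondary descriptive share are often left to a statistical analysis plan, which is not at hand, and section 5.2 does not say that the shares are unweighted. This stands in part. But the protocol writes out weighting where it intends it, leaves out the variable that its own draw forces to half, and describes the value-of-care rule in detail without either weights or a reference population. The conflict between the wording of section 1.2 and the frame of sections 2.3 and 2.5 is in the protocol text itself.

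Fourth, a reader might infer that the matching gives the non-DMP group the age, gender and utilization profile of DMP members. The protocol does not say so. Section 2.5 matches on diagnosis and lists the other three as stratification criteria, which could be applied in proportion within each sub-cohort. Section 2.1 lists disease area, gender and age group as matching criteria, but under the type of control. Such a profile is possible, not stated.

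**Conclusion.** The point holds in limited form. Research question 2 names a population that the sample cannot represent as drawn, and the protocol states no weighting for the shares that answer it or for the averages and standard deviations that define them.

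Under a fixed cut-off the pooled per-disease error is (0.5 − q)(p_DMP − p_nonDMP), between 0 and 4.5 points over the assumed range. Under a sample-relative cut-off the effect falls on the sub-cohort shares: the non-DMP low-value share is 20%, 26% or 33% at DMP fractions of 20%, 50% or 80%, given a 0.6 SD difference and ICC 0.7. The protocol supplies none of these inputs.

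Two stronger readings are not supported. One is that the trial plans no weighting at all: sections 4.1 and 5.2 plan it for the primary endpoint. The other is that the shares merely mirror the sampling quotas: the error can be zero, and equal disease sizes matter only for results pooled over diseases. As this is a secondary objective, the point calls for a correction of wording and estimation and does not question the design.

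**What to change.** - In section 5.2, state that the research question 2 shares, and the reference means and standard deviations, use design weights multiplied by a non-response weight. The design weight is the inverse selection probability by disease, DMP status and the other strata of the draw.
- Name the population to which the average refers.
- Report the unweighted DMP versus non-DMP contrast separately, as a comparison within the drawn sample.
- In section 1.2, replace the reference to Germany with the eligible insured population of the participating insurer, or justify the extrapolation.

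No new data collection should be needed: the insurer drew the sample, holds DMP participation data (section 2.6), and section 4.1 says utilization data exist for its whole population. The price is wider intervals, with a design effect of about 1.36 from DMP reweighting alone at q = 20% or 80%, and more once further weights are added.

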   1. STUDY DESIGN

The study is an observational prospective cohort study with patients of four chronic disease areas with existing DMPs (asthma, chronic obstructive pulmonary disease (COPD), diabetes (type 1 and type 2) and coronary artery disease) with two sub-cohorts (DMP and non-DMP) for each disease.

- Type of control: none / group matched BARMER insurees (matching criteria: disease area, gender, age group)
- Level and method of blinding: none
- Method of treatment assignment: stratified randomized selection of study population
- Number of subjects: 200,000 patients invited (50,000 per chronic indication and about 25,000 in each sub-cohort)
- Duration of study: one year (four quarterly survey periods)
  1. TREATMENT GROUPS

There are four disease cohorts with two sub-cohorts, each. The first sub-cohort consists of subjects participating in a DMP. The subjects of the second sub-cohort are not participating in any DMP but have a documented ICD-10-GM diagnosis of one of the selected diseases.

The ICDs of the second sub-cohorts are defined as:

- Diabetes mellitus type 1: E10, diabetes mellitus type 2: E11
- COPD: J44
- Asthmatic disease: J45
- Coronary artery disease: I25
  1. STUDY POPULATION

Inclusion criteria:

- Patient is at least 18 years old
- At least two outpatient consultations documenting a confirmed chronic disease diagnosis in 2021
- For type 1 diabetes at least one insulin prescription must be present in 2021

Exclusion criteria:

- Participation in more than one DMP

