   1. GENERAL METHODOLOGY

Quantitative variables will be described as mean (respectively median), standard deviation (inter-quartile range), number, and rate of missing data, and compared between arms with a t-test, or if not appropriate with a Wilcoxon rank-sum test. Qualitative variables will be reported as absolute and relative frequencies, number, and rate of missing variables, and compared between sub-cohorts with the Chi-square test or the Fisher’s exact test. Variables will be compared between both sub-cohorts (DMP and non-DMP participants). P-value <0,05 with a bilateral hypothesis will be considered significant. All the analyses will be carried out using R, SAS, and other statistical software for Windows.

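### The only exclusion criterion acts on the DMP sub-cohort alone, so the two sub-cohorts being compared have different eligibility rules on having several of the study diseases

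*Protocol*

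**What the plan says.** Protocol section 2.3 lists one exclusion criterion: "Participation in more than one DMP". The relevant inclusion criterion applies to everyone: "At least two outpatient consultations documenting a confirmed chronic disease diagnosis in 2021". It sets no upper limit on the number of diagnoses.

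Section 2.2 defines the two sub-cohorts. For DMP: "The first sub-cohort consists of subjects participating in a DMP". The non-DMP patients "are not participating in any DMP but have a documented ICD-10-GM diagnosis of one of the selected diseases".

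Section 2.5 describes the selection: "A one-to-one matching of participants of one DMP with non-participants of a DMP but with the same proven diagnosis". It adds: "Further stratification criteria are age group, gender, and health system utilization". The number of selected diseases does not appear.

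The comparison between the sub-cohorts is part of the general method in section 5.1: "Variables will be compared between both sub-cohorts (DMP and non-DMP participants"), by t-test, Wilcoxon, chi-square or Fisher test at two-sided 0.05. DMP membership returns as a subgroup factor in 5.1 and as a named contrast in 5.2. Section 5.2 also plans linear and logistic regressions that control for patient characteristics and other collected variables found to be significant.

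**The concern.** An exclusion defined by the number of programmes can remove only people who are in programmes. DMPs are disease-specific, so those removed are mainly people with two or more programme diseases. A person with the same two diseases who is in no programme stays eligible as a non-DMP subject. The sub-cohorts therefore differ by rule on a factor plausibly related to health scores, before any question of what a DMP does.

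At stake is how the DMP contrast is read, above all for the generic PROPr score and the disease-specific PROMs. With thousands of completers per arm, a very small built-in shift can reach p < 0.05 and be taken for a feature of programme participation.

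**Working it through.** **Sample size, reproduced from section 2.5.** 200,000 × 0.30 × 2/3 × 0.40 = 16,000, the protocol's own figure. If completion is equal across groups, this is 16,000 / 2 = 8,000 per arm pooled over the four diseases, and 16,000 / 8 = 2,000 per disease-specific sub-cohort. PROPr is asked in all four diseases. AIRQ, CCQ, PAID-5 and SAQ-7/RDS are each asked in one.

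**Assumed inputs (the protocol gives none of them).**
- m: share with two or more selected diseases before exclusion, taken as equal in both source groups
- q: share of such DMP members who are in more than one DMP and so excluded
- d: effect of multimorbidity on a score, in SD

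**Formulas.** Multimorbid share left in the DMP arm = m(1 − q) / (1 − mq). Shift towards DMP = (m − that share) × d. SE of a difference in means = √(2/n) SD.

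**Illustration: m = 0.30, q = 0.5, d = 0.5.**
- DMP share = 0.15 / 0.85 = 17.6%, against 30% in non-DMP; the gap is 12.4 points
- Shift = 0.124 × 0.5 = 0.062 SD
- n = 8,000 per arm: SE = 0.0158, z = 3.9
- n = 2,000 per arm: SE = 0.0316, z = 2.0

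**Range.** For m from 0.10 to 0.40, q from 0.2 to 1.0 and d from 0.3 to 0.5, the gap is about 2 to 40 percentage points and the shift about 0.006 to 0.20 SD.

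**What utilization stratification removes.** This was simulated with the illustration's m, q and d and 1,000,000 people per source group. Utilization was raised by 0.8 or 0.4 SD in multimorbid people, the score also fell by 0.3 per unit of the remaining utilization, and five utilization strata were used. The unstratified shift was 0.056 to 0.057 SD (slightly below 0.062 because the simulated score has an SD a little above 1). Within strata it fell to 0.028 SD (stronger link) and 0.044 SD (weaker link). The gap in multimorbid share stayed at 11 to 12 of about 12 points. The corresponding z values are:

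| Shift (SD) | z at 8,000 per arm | z at 2,000 per arm |
| --- | --- | --- |
| 0.062 (no stratification) | 3.9 | 2.0 |
| 0.044 | 2.8 | 1.4 |
| 0.028 | 1.8 | 0.9 |

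**Dependence on equal m.** Let m1 be the DMP share before exclusion and m0 the non-DMP share. The arms balance when m1 = m0 / (1 − q + m0·q). With m0 = 0.30 and q = 0.5, m1 = 0.30 / 0.65 = 46%. Above that, the DMP arm is the more multimorbid one even after the exclusion.

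**The case against.** Four objections carry weight.

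First, a reader might infer that multimorbid patients as such are removed from the DMP arm and that the comparison is therefore biased in favour of DMP. The documents do not support that. Only people in two or more programmes are removed; those with several selected diseases but one programme stay, as do those with other comorbidities. Programme membership is not randomised, and the source groups may differ before exclusion; the 46% break-even shows that the direction can reverse. This stands: only the rule's own contribution points towards DMP.

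Second, the non-DMP definition speaks of a diagnosis of one of the selected diseases, which could mean exactly one. No criterion says so, and at least one is the more natural reading. Exactly one, applied to the non-DMP arm only, would not cure the asymmetry but turn it round: under the illustration, 17.6% multimorbid in DMP against 0%, a shift of 0.176 × 0.5 = 0.088 SD against DMP.

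Third, the plan already has utilization strata and regressions, and a full covariate list is commonly left to the SAP, which is not shown. The absence of such a list is no fault. But the eligibility rule is fixed in the protocol, the tests in section 5.1 are unadjusted, and section 5.2 ties entry of covariates to significance, so a disease count is available to the models but not assured a place.

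Fourth, the study's main question is response and representativeness, DMP status is one descriptive factor among several, and no causal DMP effect is claimed. A shift of 0.03 to 0.06 SD is very small. A reader might extend the point to every cost and response-rate comparison; cost is the weaker case because utilization is a stratum, and for response rates the direction is unknown. This limits the point but does not remove the difference in eligibility.

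**Conclusion.** The point holds in limited form. The exclusion is one-sided by construction, no counterpart is stated for the non-DMP sub-cohort, and the number of selected diseases is neither matched nor stratified on. Taken alone, the rule lowers multimorbidity in the DMP arm and pushes PROM comparisons towards DMP.

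The illustrative size is about 0.06 SD before utilization stratification and about 0.03 to 0.04 SD after it in the simulated settings. It rests wholly on assumed multimorbidity, double enrolment and effect size, and on equal multimorbidity before exclusion. The larger z applies only to scores pooled over the four diseases and ignores the utilization strata, so it should not be quoted as the general risk of a spurious finding. Net size and direction cannot be derived from the protocol.

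**What to change.** - From the ICD-10-GM claims diagnoses already listed in section 2.6, derive the number of selected diseases per person, using the same 2021 two-consultation rule in both sub-cohorts.
- Pre-specify that count as an adjustment or stratification factor in every DMP versus non-DMP comparison, whether or not it is significant.
- Add a sensitivity analysis restricted to people with exactly one selected disease in both arms. It should not become the main comparison, because that would change the target population and depart from section 3, which runs all analyses on the whole study population.
- State in section 2.3 that the exclusion affects the DMP arm only, so that unadjusted differences are not read as a DMP effect, and in section 2.2 whether the non-DMP definition means at least one or exactly one selected disease.

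The cost is one derived variable, one model term and two clarifying sentences. The sensitivity analysis will use fewer patients. No new data or recruitment is needed.
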